### Outcomes

#### Primary outcomes

The primary outcomes will be feasibility, compliance, and the determination of clinically relevant taVNS treatment effects. Feasibility will include recruitment and retention rates, randomization success, blind-success, compliance with questionnaires and assessment procedures and the occurrence of any adverse events (Table 2). The compliance of 4 h/day taVNS will be electronically logged by an app on the patient’s smartphone. Treatment is considered to be compliant when at least 80% of patients use the stimulator for at least 2 h (mean) per day. Furthermore, this study was designed to detect clinically relevant treatment effects, which we consider to correspond to statistically large effects according to Cohen [47]. An established and widely used, validated questionnaire will be applied to assess the pain severity and activity limitations (GCPS (Graduation of Chronic Pain according to Von Korff [44])).

**Table 2 Tab2:** Key feasibility indicators for progression [48, 49]

Key indicator	Go—proceed with RCT	Amend—proceed with changes	Stop—do not proceed unless changes are possible
**Recruitment rate** *Target figure: 20 participants*	≥ 70% of target number	51–69% of target number	≤ 50% of target number
**Retention rate** *75% of the participants randomized to intervention group will complete outcome measures T0, T1, and T2*	≥ 70% of target number	51–69% of target number	≤ 50% of target number
**Compliance**	≥ 80% of target number use the stimulator for at least 2 h (mean) per day	61–79% of target number use the stimulator for at least 2 h (mean) per day	≤ 60% of target number use the stimulator for at least 2 h (mean) per day

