According to power calculations done with G*Power 3.1.9.7 and assuming an alpha error level of 5%, a power of 95%, and a moderate correlation among repeated measures (*r* ≥ 0.5), a sample size of *n* = 18 is required to detect significant intervention (stimulation vs. sham) × time (visit 0, visit 1, visit 2) interaction effects of this size. Assuming a drop-out rate of approximately 10%, a sample of *n* = 20 participants will be initially recruited, 10 in each of the two groups “sham” and “stimulation.” Another just-conducted pilot trial on a taVNS intervention also reaches clinically relevant effects with a similarly small sample size [50]. Furthermore, an investigation of taVNS application in fatigue syndrome reported highly significant effects (*p* < 0.0003) with a sample size of *n* = 15 [51]. Other studies evaluating taVNS application in migraine also used samples of 20 to 30 patients [52–54]. Consequently, a sample size of *n* = 20 appears to be sufficient to achieve statistical significance for clinically relevant (i.e., large) effects of taVNS and was therefore adopted in this study.

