### End of study

#### Data analysis

This trial features a 2 × 3 factorial design with the factors group (stimulation, sham) and time (Visits 0, 1, 2). Main and interaction effects on the secondary endpoints will be statistically tested via a mixed-measures ANOVA. In case the preconditions for ANOVA use are not met, nonparametric alternatives will be employed. Global effects will be further elucidated by appropriate post hoc comparisons between individual conditions (i.e., per group or time point). The significance threshold will be set to *p* < 0.05, corrected for multiple comparisons where needed. Furthermore, estimates of treatment effect size and confidence intervals will be reported in addition to significance testing results. These analyses will provide a treatment effect estimate on each outcome measure. Outcome measures at baseline, 4 and 8 weeks post-intervention will be entered into the model as the dependent variables with fixed effects of study arm, baseline outcome measures, time, and time point by study arm interaction.

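### The analysis model uses the baseline value as both outcome and covariate, which makes the adjusted week-4 arm difference look about 15% too precise; the group × time interaction is unaffected

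*Protocol article*

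**What the plan says.** The Data analysis section of the protocol article opens with a 2 × 3 design, naming the "factors group (stimulation, sham) and time (Visits 0, 1, 2". Main and interaction effects are to be tested by mixed-measures ANOVA, with follow-up comparisons by group or time point. Effect sizes and confidence intervals are promised for each outcome measure.

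The paragraph closes with a model specification: "Outcome measures at baseline, 4 and 8 weeks post-intervention will be entered into the model as the dependent variables". For the predictors of that same model, the sentence goes on to name "fixed effects of study arm, baseline outcome measures, time, and time point by study arm interaction". Baseline is therefore a level of the response (Visit 0) and also a predictor in the same model. Nothing in the article says that the Visit 0 record is left out when baseline is the covariate, and no baseline × time term is listed.

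The sample size in the Primary outcomes section rests on the intervention × time interaction over Visits 0, 1 and 2, with "a moderate correlation among repeated measures (*r* ≥ 0.5".

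**The concern.** At Visit 0 the closing model regresses the baseline on itself, so the slope there is 1; at the follow-up visits the true slope is the within-patient correlation. One common slope has to compromise between the two. It leaves small residuals at Visit 0 and inflated ones at follow-up. If a single variance is then applied to all visits, the follow-up variance is understated, and so is the standard error of the adjusted arm difference at week 4.

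A second matter is independent of the covariate. With Visit 0 as an outcome level, the arm main effect averages over a visit at which treatment has not begun.

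What is at stake is the estimates and intervals that this section promises, which the Objectives section says will inform a larger trial. Two different models in one paragraph also leave the choice open until the data are seen.

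**Working it through.** **1. The plan's own sample size.** Inputs from the Primary outcomes section: "assuming an alpha error level of 5" percent, power 95%, three visits, two arms, r = 0.5. The effect is described only as large ("which we consider to correspond to statistically large effects according to Cohen [47"); f = 0.40 is my assumption. For the within–between interaction:

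- λ = f²·N·m/(1 − r) = 0.16 × 18 × 3/0.5 = 17.28
- df1 = (2 − 1)(3 − 1) = 2; df2 = (18 − 2)(3 − 1) = 32
- Power = 0.953 at N = 18 and 0.924 at N = 16, so the minimum is 18
- 18/(1 − 0.10) = 20

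The stated 18 and 20 reproduce.

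**2. Week-4 arm difference in the model with baseline on both sides.** Assumptions: SD 1 at each visit, equal correlation r between visits, one common baseline slope, random intercept, constant variance. At r = 0.5:

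- Common slope b = (1 + 2r)/3 = 0.667 (the follow-up slope alone would be 0.50)
- Residual variance at Visit 0: (1 − b)² = 0.111
- Residual variance at Visit 1: 1 − 2br + b² = 1 − 0.667 + 0.444 = 0.778
- Variance the model applies at every visit: (0.111 + 0.778 + 0.778)/3 = 0.556
- SE ratio: √(0.556/0.778) = 0.845, about 15% too small
- Large-sample coverage of a nominal 95% interval: 2Φ(1.96 × 0.845) − 1 = 90.2%

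Over other correlations, large-sample coverage is 90.9% at r = 0.3 and 89.5% at r = 0.8.

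**3. Simulation at the trial's size (random-intercept REML).**

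| Setting | Model SE | Empirical SE | Coverage |
|---|---|---|---|
| 10 per arm, r = 0.5, residual df | 0.337 | 0.393 | 90.4% |
| 10 per arm, r = 0.5, 17 df | 0.337 | 0.393 | 92.0% |
| 9 per arm, r = 0.5, N − 3 df | 0.354 | 0.418 | 92.1% |
| Week-4 ANCOVA, 10 per arm, r = 0.5 | 0.397 | 0.396 | 94.9% |
| All visits, no covariate, 10 per arm, r = 0.5 | 0.447 | 0.443 | 94.9% (residual df) |

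Type I error in the 9-per-arm runs was 8.0% at r = 0.5 and 8.6% at r = 0.7. A separate set of runs gave 8.3% and 8.7%. The week-4 point estimate is not biased (0.80 for a true 0.80).

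**4. Group × time contrast (Visit 1 minus Visit 0).** The covariate term b × baseline cancels in the difference, leaving variance 2(1 − r) = 1.0. The model's value is twice its within-patient variance of 0.5, also 1.0. The SE ratio is 1.00 and simulated coverage is 95.0%.

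**5. Arm main effect.** With effects d4 and d8 at the two follow-up visits, the main effect is (0 + d4 + d8)/3 and the mean post-baseline effect is (d4 + d8)/2. The ratio is 2/3 whatever d4 and d8 are.

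- Effect 0.80 at both visits: 1.60/3 = 0.53 against 0.80 (simulated 0.535)
- Effect 0.80 at week 4 and none at week 8: 0.80/3 = 0.27 against 0.40 (simulated 0.268)

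Without the covariate the simulated main effect is the same size (0.533), so this follows from Visit 0 being an outcome level and not from using baseline twice.

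**The case against.** Four points weigh on the other side.

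- **The interval result depends on structure that the article does not fully state.** No covariance structure is given. If baseline had its own slope at each visit, as in a multivariate repeated-measures ANCOVA, the week-4 estimate would equal ordinary ANCOVA; simulated coverage is then 95.0% at r = 0.5 and 95.1% at r = 0.7. Simple between-arm tests at one visit would also be valid. This stands, and it makes the 15% conditional. But the listed fixed effects contain no baseline × time term, so the common slope is the literal reading. An unstructured covariance alone does not rescue the common-slope model: a slope of 1 fits the Visit 0 record perfectly and the likelihood degenerates.
- **The powered test is sound.** A reader might infer that all tests are anti-conservative, or that n = 18 fails. Step 4 shows otherwise.
- **The dilution has another cause and a limited effect.** A reader might attribute the one-third shrinkage to the double use of baseline. It occurs equally in the plain 2 × 3 ANOVA. In the covariate model the main effect is exactly 2/3 of the ANCOVA estimate, and its sampling SD shrinks by the same factor (0.218 against 0.327), so its test loses essentially no power there. The article also nowhere names the arm main effect as the treatment estimate.
- **No progression rule uses the interval.** Table 2 decides on recruitment, retention and compliance only. This limits the consequence, although treatment effect on pain is a listed primary outcome.

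It would also be too strong to call the Visit 0 residuals negligible: at r = 0.5 their variance is 0.111, one seventh of the 0.778 at follow-up.

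**Conclusion.** The model specification is wrong as written: baseline cannot be both a response level and a common-slope covariate in one model, and the same paragraph describes a different model without the covariate. With one common slope and a constant-variance random intercept, the adjusted week-4 arm difference has an SE about 15% too small at r = 0.5. Coverage is about 90–92%, depending on the degrees of freedom, and type I error is about 8% with N − 3 degrees of freedom. These figures assume equal correlations and equal variances across visits, and a visit-specific baseline slope would remove the problem.

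The group × time interaction and the sample size stand. Separately, in both models the arm main effect is two thirds of the mean post-baseline effect; it misstates the size of the effect if reported as the treatment estimate.

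**What to change.** State one model in the Data analysis section. Either of these resolves the contradiction:

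- **(a)** Outcomes at Visits 1 and 2 only, with arm, visit, arm × visit and baseline as fixed effects. Report the arm difference with its 95% confidence interval at each visit.
- **(b)** All three visits as outcomes, with the baseline value removed from the fixed effects. Report the time × arm contrasts (change from Visit 0 to Visit 1, and from Visit 0 to Visit 2) as the treatment effects, with 95% confidence intervals.

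Option (b) matches the interaction on which the trial was sized. Option (a) gives an adjusted estimate at each visit. If all three visits are kept, say that the arm main effect is not the treatment-effect estimate. A baseline × visit term and an unstructured covariance are optional refinements under (a).

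The cost is the rewording of one paragraph before analysis. No new data, visits or patients are needed.

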## Discussion

The strength of this protocol is the novelty of investigating taVNS as a potential, well-tolerated, and safe treatment option [33] for patients with chronic TMD symptoms. Further advantages of taVNS are that it can be combined with other treatment options, like splint-, physical- or pharmacotherapy, without risking adverse side effects. Moreover, due to its ear pod-style design, patients may continue their routine activities, facilitating a high treatment compliance [38].

Several studies are available in which healthy participants were subjected to an acute taVNS. Importantly, none of the studies reported an occurrence of relevant side effects in the short or longer run [34, 39, 62, 63]. Only nausea, skin irritation of the ear, and worsening of preexisting tinnitus were observed. The drop-out rate associated with side effects was only 2.6% [64–66].

Due to the complexity of the etiology, the diagnosis and treatment of TMD remain a challenge [21]. A high vagal activity has been considered to improve the psychological health and is hypothesized to have therapeutic potential in a wider spectrum of illnesses [34, 43]. Since vagus nerve stimulation has already been investigated successfully for several other acute and chronic pain disorders with similarities in the pathophysiology of TMD, including migraine, depression, tinnitus, and fibromyalgia [39], a response to the innovative and gentle therapy option of taVNS is possible. Potentially, taVNS could also give chronic TMD pain patients a significant gain in their quality of life, which makes its non-invasive application justifiable.

Potential limitations of the present study include that the taVNS requires the active patient cooperation compared to an implantable VNS [35]. However, due to the practical design of taVNS and the high level of suffering of TMD patients, the patients’ compliance should be high. A further limitation is the single-blinded study design. A future definitive trial should be double-blinded with an independent dentist performing the device instructions and blinded outcome assessors. Furthermore, results will only reflect short- or mid-term effects as the treatment duration will be only 4 weeks [40]. Future studies should also investigate long-term effects.

## Data Availability

As this is a report of our trial protocol, no data is available yet.

## Abbreviations

DC/TMD: Diagnostic criteria for temporomandibular disorders
EMG: Electromyography
FDA: Food and Drug Administration
GAD: Generalized Anxiety Disorders
GCPS: Graduation of Chronic Pain
iVNS: Invasive vagus nerve stimulation
NSAIDs: Nonsteroidal anti-inflammatory drugs
OHIP: Oral Health Impact Profile
PHQ: Patient Health Questionnaire
RCT: Randomized controlled trial
TMD: Temporomandibular disorders
TMJ: Temporomandibular joint
taVNS: Transcutaneous auricular vagus nerve stimulation
VNS: Vagus nerve stimulation
WHO: World Health Organization
